## **List of Assessments**

### **Adolescent Measures**

**Demographic Information:** Demographic information will be obtained at baseline from adolescents and parents using the General Information Sheet (GIS) covering age, date of birth, sex, height, weight, address, phone number(s), email address(s), race/ethnicity, school placement, parental marital status, family composition, number of siblings and first-born status, and number of lifetime moves, and, derived from the Four-Factor Hollingshead measure of social status.

**General Information Sheet** – Adolescents and parents will provide demographic information about themselves at baseline and follow-up assessment points. Information collected includes age, date of birth, sex, height, weight, address, phone number(s), email address(s), race/ethnicity (teen only), school placement (teen only), parental marital status (teen only), family composition (teen only), number of siblings and first-born status (teen only), and number of lifetime moves (teen only) derived from the Four-Factor Hollingshead measure of social status.

**KSADS** – The KSADS is a semi-structured clinical interview that is used to assess psychiatric diagnoses in participants under age 18, specifically for depression and anxiety, and provides screening interviews for bipolar disorder and psychosis. This instrument is used to interview both the child and the parent about the child's current and past psychiatric diagnoses.

**KLIFE** – This instrument will be used to assess these same diagnoses since baseline and will be administered to both children and parents at the 2, 6, 12 and 24 month follow-ups. The KLIFE measures the occurrence, degree of severity of new episodes, and the extent of impairment using the Depression Rating Scale (DRS), which yields a depression score from 1-6 for each week of the follow-up interval.

**CES-D** – The Center for Epidemiological Studies – Depression Scale is a self-report measure of the frequency of 20 depressive symptoms over the past week, using a 5-point scale. The use of self-report scales like the CES-D as depression case-finding or screening instruments has been successfully validated with both adults and adolescents. The CES-D is short and easy to read, has been successfully administered in several large adolescent school samples, and has strong psychometrics with youth.

**SCARED** – The SCARED is a 41-item scale, with five factors corresponding to different diagnostic categories of anxiety, and with good reliability and validity. Anxiety is often comorbid with depression and may predict either a better or worse response to the intervention.

**DBD** – The Disruptive Behaviors Disorder Scale is a self-report measure assessing the level of teens' behavioral problems.

**Beck Hopelessness Scale (BHS)** - This is a 20-item, true-false measures the extent to which individuals are pessimistic about their future. The BHS has been shown to predict dropout from psychosocial treatment and poorer treatment response. The BHS has strong psychometric properties in adolescent samples.

**Conflict Behavior Questionnaire** - A self report questionnaire evaluating relationship experiences and conflict between parent and child (both mother and father)

**World Health Organization (WHO) Quality of Life Scale** – This is a 26-item scale to assess an individual's perceptions regarding their quality of life within the context of their culture and value system, personal goals, standards, and concerns.

**Sibling Relationship Questionnaire (SRQ)** – A self-report measure containing 48 questions evaluating sibling relationships and support.

**Social Adjustment Scale (SAS)** – A self report measure containing 36 items. The measure is designed to evaluate behaviors at school, with peers, and at home over the past two weeks.

**Teen Behavior Questionnaire (TBS)** – a self report questionnaire regarding diet, exercise, religion, and internet use.

**CRAFFT** – This is a 6-item measure that assesses non-alcohol illicit substances.

**ALEQ (life events)** – The Adolescent Life Events Questionnaire is a retrospective self-report measure that asks the teen to report on the presence/absence of various life events in the following categories: health/loss, conflict/arguments, changes/moves, school/job, finances, and crime and legal issues.

**Theory of Planned Behavior Scale** – We adapted the items from a previous questionnaire that was adjusted based on the preventive health model. The original instrument, developed for prostate cancer, was adapted to

primary care based depression prevention. The participants will indicate a level of agreement based on a Likert-type scale of 1=strongly disagree, 2=disagree, 3=neither agree nor disagree, 4=agree and 5=strongly agree with items such as “depression intervention makes sense to me.”

**Trans-theoretical Model Scale** - We will measure motivation to change risk-factor behaviors before, during, and after the intervention. We adapted the standard approach for measuring motivation as described by Miller and Rollnick to evaluate importance (“rate the importance of preventing a depressive episode”), self-efficacy (“rate your ability to learn coping skills to reduce your risk of depression”) and readiness (“rate your readiness to learn coping skills”) on a 1-10 scale (1, “not important”, 10 “very important”).

**Child’s Report of Parental Behavior Inventory (CRPBI)** – A scale used to evaluate a teen’s perceptions and experiences of both mother and father.

**Sibling Inventory of Differential Experience (SIDE)** – A scale to measure a teen’s perceptions of parent (both mother and father separately) responses to the teen as compared to their siblings.

**Motivational Interview Pre-Measure** - This measure is administered to adolescents prior to meeting with the physician for a motivational interview. It contains items asking adolescents to identify goals for the intervention, consider how they are feeling and their degree of motivation to change their feelings, and their willingness to engage in the present intervention. This is an optional measure.

**Suicide Ideation Scale** - A scale used to assess the adolescent’s current level of suicidal tendencies. This measure is only used in response to adolescent reports of suicidal thinking.

**Suicide Intent Scale** – A measure used to inquire about past suicide attempts. This measure is only used in response to adolescent reports of suicidal thinking.

**Lethality Scale** – A measure of the lethality of past suicide attempts. This measure is only used in response to adolescent reports of suicidal thinking.

**Safety phone calls-** Assessment calls to evidence self-harm ideation and adverse experience with Internet program. Qualitative questions regarding website and baseline interview are also included.

### **Parent Measures**

**KSADS** - Please see description above.

**KLIFE** - Please see description above.

**CES-D** - Please see description above. Parents will complete the CES-D regarding their own mood, and also will complete the CES-D about their adolescent.

**Conflict Behavior Questionnaire** - A self report questionnaire evaluating relationship experiences and conflict between parent and child

**DBD** – The Disruptive Behaviors Disorder Scale is a self-report measure assessing the level of teens’ behavioral problems.

**Child’s Report of Parental Behavior Inventory - Parent (CRPBI)** – A scale used to evaluate a parent’s perceptions and experiences of their child.

**Sibling Relationship Questionnaire (SRQ)** – A self-report measure containing 48 questions evaluating sibling relationships and support.

**World Health Organization (WHO) Quality of Life Scale** – This is a 26-item scale to assess an individual's perceptions regarding their quality of life within the context of their culture and value system, personal goals, standards, and concerns.

**Suicide Ideation Scale** - Please see description above. This measure is only used in response to adolescent reports of suicidal thinking.

**Suicide Intent Scale** - Please see description above. This measure is only used in response to adolescent reports of suicidal thinking.

**Lethality Scale** - Please see description above. This measure is only used in response to adolescent reports of suicidal thinking.

**The Child and Adolescent Services Assessment (CASA):** This measures use of medical services by adolescent.

### **Physician/Nurse Measures**

**Physician and Nurse Feasibility Questionnaire:** We developed a physician and nurse feasibility instrument based on interviews with providers and primary care observation (willingness used with permission of [name]). We developed these measures based on the [name] practice experience and discussions with office staff. They were then used to evaluate practice experience with the intervention in the recently completed randomized trial. Willingness and capability predicted practice performance of key functions such as screening.

**Feasibility** ( $\alpha=0.83$  for physicians,  $0.94$  for nurses): This construct was developed to gather information regarding specific elements of the program. Providers were asked to provide answers to each statement using a five-point scale from 1 (strongly disagree) to 5 (strongly agree). Physicians and nurses are surveyed on elements of the process to screen for depression, and about the motivational interviewing process and the Internet modules. Group means and standard deviations for each statement are generated.

**Willingness** ( $\alpha=0.86$  for physicians,  $0.78$  for nurses): Physicians and nurses provide opinions regarding the responsibility of primary care providers to care for adolescent depression. Each statement begins with "I believe that primary care providers should. . ." followed by a statement (e.g., "ask directly about depressive symptoms during well-child visits"). Statements are rated on the five-point scale from 1 (strongly disagree) to 5 (strongly agree). Group means and standard deviations for each statement are generated.

**Capability** ( $\alpha=0.77$  for physicians,  $0.78$  for nurses): Providers are asked to provide opinions regarding their abilities to provide depression-related services to patients (e.g., "I have adequate knowledge about adolescent depression"). Providers answer on a five-point scale from 1 (strongly disagree) to 5 (strongly agree), with group means and standard deviations generated for each statement.

**Sustainability** ( $\alpha=NA$ , only one item): On a five-point scale from 1 (strongly disagree) to 5 (strongly agree), providers are asked, "I would implement the entire program (interview and referral to Internet website) in my office even if I were not enrolled in the study." Nurses were asked additionally, "I would recommend the intervention to my child or the child of a close friend." Group means and standard deviations are generated for each statement. The implementation statement also serves as the outcome measure for the willingness and capability statements.

**Medical Home Safety Net Scale: Assessment, recently developed at the University of Illinois at Chicago, measures practice adherence to the medical home model.**

**M. Quality assurance over assessment.** Interviewers will have extensive clinical experience with adolescents and with administration of the Kiddie Schedule of Affective Disorders (K-SADS). A computer-based algorithm (Chicago) will determine periodicity of assessments. We estimate the total time for each phone assessment to be 30 minutes and total assessment time to be < 2 hours, which is substantially less than the total duration of activity time with the intervention (1 hour provider, 3 hours Internet).

**N. Incentives to participants.** Adolescent and parent participants will receive small monetary incentives to compensate them for their time and travel expenses (\$200 over 2 years to adolescent, \$100 over 2 years to parent). Participants will also receive reimbursement for travel up to \$20 in value. Physicians will be compensated through their practices based on pro-rated reimbursement (to practice) for time devoted to study participation (training, interviews etc) at \$200 for each HEALTH EDUCATION participant and \$400 for each CATCH-IT participant. Nurses and medical assistants will receive \$100 over 2 years. Should the participant not wish to receive a cash payment, be unable to collect a payment in person, or prefer a payment be mailed, incentives will be mailed or emailed to the participant in the form of check or gift card. Small gift cards (valuing \$5) will be provided to teen participants for module completion (valuing \$20 in total). These will be mailed to each participant. When teens turn 18 years old in the study, they need to sign reconsent forms to continue their participation. If teens wish to continue in the study, they will receive \$50 for signing their consent and HIPAA forms. This can be given to them in the form of cash or a giftcard. Teens will receive an additional \$35 in the form of a Tango gift card for completing qualitative questions about their experience with the PATH study after 24 months.

| Time (month) | Key Task                 | Milestone                                                             |
|--------------|--------------------------|-----------------------------------------------------------------------|
| 0-6          | Study preparation        | Training of sites and final functional tests of Internet intervention |
| 7-12         | Start-up all sites       | Enroll N=80                                                           |
| 13-24        | Enrollment               | Enroll N=160 total N=240                                              |
| 24-30        | Enrollment and follow-up | Enroll N=160, total N=400, complete follow-up N=80                    |
| 30-42        | Follow-up completion     | complete follow-up N=80, complete follow-up N=80, total N=160         |
|              |                          | complete follow-up N=80, total N=240                                  |
| 36-48        |                          | complete follow-up N=80, total N=320                                  |

**i. Data analysis:** Descriptive statistics will be calculated for the variables. As appropriate, the Pearson chi-square test, Fisher's exact test, or analysis of variance will compare the CATCH-IT 3 and HEALTH EDUCATION groups for balance on baseline characteristics, including demographics and prior treatment history. While randomization should be successful, any variables significantly differing between groups will be included as a covariate in the analyses, along with those we expect to be related to depressive disorder (i.e., gender), and those we find to be empirically related. STATA, SPSS, SAS, and Mplus will be used for the analyses.

**Survival analyses:** We will test for constant hazard over time and if not significant at 0.10 will use Cox proportional hazards to compute the hazard ratio for major depressive episodes for the intervention group in comparison to the HEALTH EDUCATION group. If the test or diagnostics reveal non-proportional hazards, i.e. there is evidence of differential effect over time, i.e. 1-year vs 2-year outcomes; we will include this non-proportionality in analyses. We have used such limited "model fitting" tests without regard to the magnitude of intervention effect in previous analyses that still preserve the Type I error rate, and will follow multiple comparison procedures we have previously used to identify time intervals where significant effects are found.

**Longitudinal data analysis:** Our general method will be to use growth curve modeling with continuous outcomes to examine how the intervention changes depressive symptoms, vulnerability factors, educational impairment and quality of life. Simple comparisons will be calculated as appropriate (e.g. number of depressed days), and survival curve modeling will be used for binary outcomes for prevalence of disorders. Guided by our methods development on growth models, we will address missing data using full information maximum likelihood and multiple imputation, which provide improvement over "last observation carried forward" and other less refined methods. We will also examine whether there are variations in growth trajectories by introducing covariate interactions and mixtures to growth models, techniques that we and our colleagues have developed. These more complex models can characterize quantitatively differential response as well as qualitative changes such as recurrence. All such models will be preceded by careful model checking.

**Mediator analysis:** We will evaluate potential mediators including change in motivation, principles (intervention experience characteristics) of effective preventive interventions (adherence/dose, positive relationships, training and socio-cultural relevance) and changes in vulnerability and protective factors (social support, automatic negative thoughts, depressed mood). Based on our recent work on a comparison of analytic models for mediation with nonlinear models, we will use the "product of coefficients" method to conduct tests of mediation and the bootstrap method for accurate confidence intervals. To examine the effects of participating in the website, we will conduct complier average causal effect (CACE) analyses that include covariates predicting participation status.

**Moderator analysis:** We expect to conduct tests of moderation in six domains: (1) demographic and cultural factors, (2) vulnerability factors and adverse events, (3) motivation and attitudes, (4) physician relationship, (5) parent and child co-morbid psychopathology, and (6) treatment before and during study. We will use sub-group analyses and tests of interaction to evaluate moderator effects.

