## e. Description of Procedures

**Random assignment to experimental conditions:** Participants will be assigned randomly to CATCH-IT 3 or HEALTH EDUCATION. Randomization will be blocked by practice and stratified by level of risk, and will be balanced across time. Blocked randomizations will be prepared by the Northwestern site (data analysis site).

Intervention

- I. CATCH-IT 3 intervention defined.** Based on promising results from the phase 2 trial of CATCH-IT 3, a modified version of this primary care/Internet-based preventive intervention is being prepared (text revised and edited, Internet design completed,) titled CATCH-IT 3 revised (CATCH-IT 3), using previously published methods. The CATCH-IT 3 intervention has a motivational (3 PCP motivational interviews at time 0, 2 months and 12 months and 2 check-in phone call at week 1 and week 4 ) and an Internet component (with separate adolescent [14 modules] and parent [5 modules] programs). Parents have a parallel structure of motivational (3 motivational interviews at time 0, 2 months and 12 months, performed by study coordinator) and 2 phone calls at weeks 1 and 4 after enrollment) This revised and expanded intervention will include a comprehensive approach to reducing modifiable risk factors and enhancing resiliency factors associated with increased or decreased risk of depression, respectively, proposed by Spence and [name]. Study staff will monitor time in study and deploy elements of the intervention based on time since enrollment, including computer and human elements (e.g. calls, doctor visits). If study staff are unable to reach participants by phone on the first attempt for any of the above mentioned study procedures, staff will attempt to call two (2) more times over a 1-2 week period to establish contact. If no response is received, staff will try contacting participants by a secondary method as specified in the General Information Sheet (email, mail, or text message). Staff will then wait 2 weeks before contacting the participant again. This process will be repeated until contact with the participant is made or the participant requests to be withdrawn from the study. If withdrawal is requested, a letter confirming their withdrawal will be sent. Details regarding contact of participants and withdrawal procedures can be found in the **Protocol for Contacting Participants and Withdrawal Procedures**.

[figure not shown]

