## **Sample Size and Statistical Power**

**Aim 1:** We conducted a series of power/sample size calculations through a SAS macro ([name], 1995) under realistic alternatives to address impact on MDE. We require 200 randomized subjects per intervention condition to achieve 80% power based on a conservative application of our pilot study findings from the CATCH-IT trial. These calculations assume that in the control group 72% are free from depression after one year follow up and the second year continues to follow the same exponential rate for controls; for intervention the hazard is a constant ratio of 0.62, and an attrition rate of 7% for each of the first 4 quarters and 2% for each of the second 4 quarters. Note that the estimated hazard rate of 0.62 is 2/3 of that we observed in this previous study. There are concerns raised about the use of pilot study data to assess power, even using a

lower value than we observed, so we conducted other power calculations based on the data from a similar study. In their study, they found a departure from exponential and disproportional hazards of intervention over time. Assuming the same attrition rate as we found above, a study with 400 randomized subjects would produce 80% power when the effect of CATCH-IT 3 was only 60% at every interval of time relative to the CBT hazard rate in the Clarke's study. Thus we expect to have sufficient power even if the overall benefit is 60% that obtained by Clarke.

**Aims 2 and 3:** We will examine changes in the growth curve for depressive symptoms and quality of life over 6 measures. We have 80% power to detect a modest effect size of 0.25 by the last time point, accounting for 75% reliability in the intercept ([www.psmg.usf.edu/PowerCal/case0.html](http://www.psmg.usf.edu/PowerCal/case0.html)).

**Aim 4:** Using mean and standard deviation values from our previous educational impairment data as an illustration of moderator analyses with M=11.3 (SD=3.6) and M=9.9 (SD=3.4), with power of 0.80, alpha level of 0.05, and 10% attrition, 109 participants are needed for each group for a total of 218 participants. Thus we have sufficient power to detect moderate to large interactions with intervention.

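### Covariates are chosen partly by balance tests and an undefined empirical criterion, and the randomisation factors are not named in the analysis model

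*Protocol*

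**What the plan says.** The Data analysis section compares the arms by chi-square, Fisher's exact test or analysis of variance, testing the "groups for balance on baseline characteristics, including demographics and prior treatment history". It then builds the covariate set from three sources:

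- **Imbalance:** "any variables significantly differing between groups will be included as a covariate in the analyses".
- **Expectation and association:** "along with those we expect to be related to depressive disorder (i.e., gender), and those we find to be empirically related".

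The second item holds two sources. One is prior expectation, with gender as the only named variable. The other is association seen in the trial's data. The section gives no list of candidate variables, no significance level for the balance tests and no criterion for empirical association. The rule is written for the analyses in general, so it reaches the Aim 1 model, which uses "Cox proportional hazards to compute the hazard ratio for major depressive episodes for the intervention group".

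Under Random assignment to experimental conditions, the design is described thus: "Randomization will be blocked by practice and stratified by level of risk, and will be balanced across time". Neither practice nor level of risk is named as a covariate, stratum or random effect in the survival or longitudinal analysis paragraphs.

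**The concern.** When allocation is random, a significant baseline difference is a chance event. It says nothing about whether the variable predicts depressive episodes, so the balance test selects on the wrong property. The clause "and those we find to be empirically related" has the opposite weakness. It does aim at prognostic variables, but it uses outcome data, and without a stated test, threshold or candidate list two competent analysts could reach different primary models.

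The variable that the design itself treats as prognostic, level of risk, has no assured place in the model. Baseline CES-D and past depressive episode (from the K-SADS interview) also have none, although the protocol's own preliminary work reports that greater depressed mood predicted higher risk.

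At stake are the credibility of the primary p-value and some efficiency in a trial planned at 80% power with little slack.

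**Working it through.** **1. The plan's own power figure.** Inputs from Sample Size and Statistical Power: "We require 200 randomized subjects per intervention condition to achieve 80% power"; "in the control group 72% are free from depression after one year follow up", with the same exponential rate in year 2; constant HR 0.62; attrition of 7% per quarter in year 1 and 2% per quarter in year 2. Two-sided alpha of 0.05 is assumed, because none is stated for Aim 1.

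- Control hazard: −ln(0.72) = 0.3285 per year. Intervention hazard: 0.62 × 0.3285 = 0.2037.
- Attrition as a competing hazard: −4 ln(0.93) = 0.2903 per year in year 1; −4 ln(0.98) = 0.0808 in year 2.
- Expected events over two years: 78.0 control + 53.8 intervention = 131.8.
- Schoenfeld power: Φ(|ln 0.62| × √131.8 / 2 − 1.96) = Φ(2.744 − 1.96) = 78.4%.

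With attrition at the end of each quarter, 135.3 events give 79.4%. The stated 80% is reproduced to within 2 points; exactly 80% needs 138 events.

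**2. Chance flags from the balance tests.** With k independent variables tested at 0.05, P(at least one flag) = 1 − 0.95^k.

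| k | P(at least one) |
|---|---|
| 10 | 40% |
| 15 | 54% |
| 20 | 64% |

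The protocol gives neither k nor the level. The General Information Sheet alone supplies about a dozen analysable items, before the baseline scales in Table 5, so 10 to 20 is a plausible range.

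**3. What the rule does to the Cox model.** 2,500 trials per scenario were simulated with N = 400 and the rates and attrition above, in permuted blocks of 4 within practice by risk level. Assumptions not in the protocol:

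- 40 practices;
- 12 candidate covariates, 2 of them prognostic;
- selection at p < 0.05;
- two settings: risk-level HR 2 with practice SD 0.3 on the log hazard, and risk-level HR 3 with practice SD 0.5.

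In the rows for the protocol's rule, gender enters along with any variable that is imbalanced or associated with outcome. Practice was not modelled in any fit.

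True conditional HR 0.62:

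| Model | Power (HR 2 / HR 3) | Mean HR (HR 2 / HR 3) |
|---|---|---|
| Unadjusted | 70.2% / 67.3% | 0.656 / 0.672 |
| Gender + risk level only | 72.5% / 71.6% | 0.646 / 0.654 |
| Protocol's rule, risk level not entered | 74.3% / 71.1% | 0.636 / 0.657 |
| Protocol's rule + risk level | 76.3% / 75.7% | 0.627 / 0.637 |

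The gain from adding risk level to the rule is 76.3 − 74.3 = 2.0 points and 75.7 − 71.1 = 4.6 points.

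True HR 1:

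| Model | Two-sided rejection (HR 2 / HR 3) | Mean model SE against empirical SD (HR 2; HR 3) |
|---|---|---|
| Protocol's rule, risk level not entered | 4.5% / 3.8% | 0.158 against 0.157; 0.157 against 0.148 |
| Protocol's rule + risk level | 5.5% / 4.6% | 0.159 against 0.161; 0.157 against 0.155 |

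Mean HR was 1.00 in all four cells. The simulation error on a 5% rate is √(0.05 × 0.95 / 2500) = 0.4 points, so nothing here shows inflation. The standard error is visibly too large only in the risk-HR-3 setting without risk level.

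**4. Room for choice.** Taking the most favourable of five covariate sets in each null trial moved the mean HR to about 0.97. Two-sided rejection stayed at 4.5% and 3.6%, but a two-sided rate counts both directions and does not show how often the choice favours the intervention.

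**The case against.** The strongest reply is that the open clauses would do most of the work. Level of risk, CES-D and past episode are just what an analyst would expect, or find, to be related to depression, and nothing in the protocol excludes them. A reader might infer that the randomisation factors and main predictors are left out of the model. The text supports only that they are not named.

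A reader might also infer a large power loss. If baseline risk has SD 0.8 on the log hazard, an unadjusted model has 63% power against 75% adjusted; with SD 0.5 it is 74% against 79%. But the protocol plans no unadjusted primary model. In a further simulation of 800 trials per setting, a single measured risk score that entered only if associated with outcome at p < 0.05 was selected every time, and power matched the adjusted model (77% at SD 0.5, 75% at SD 0.8). Several weaker predictors would be selected less reliably, so this limits the loss without removing it.

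A third tempting inference is that the rule biases the result or inflates type I error. The null simulations do not support it. The drift toward 1 under a real effect is the usual attenuation of a conditional HR when a prognostic factor is omitted. Nor does adjusting for a chance-imbalanced covariate bias the HR, so the 40% to 64% describes an arbitrary selection, not a harm in itself.

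Two further points stand. The main analyses are assigned to a site that does not deliver the intervention, which is a partial safeguard. And a full covariate list and the handling of practice could properly sit in a statistical analysis plan; their absence alone would not be a finding. What remains is that the protocol states a selection rule, and states a poor one. A later plan could repair it only by departing from the protocol.

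**Conclusion.** The point holds as a badly chosen rule. Covariates are selected partly by tests that find chance differences and partly by a criterion that is not defined, and the primary model is left open to avoidable choice. There is no evidence of type I inflation or of bias under the null when the rule is applied mechanically.

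If risk level does not enter, the cost is about 2 to 5 power points, a mean HR of about 0.64 to 0.66 against 0.62, and standard errors up to slightly too large. These sizes depend on the assumed risk-level HRs of 2 to 3 and the other simulation settings. No figure supports a separate claim about clustering by practice. The mixing of first and recurrent episodes, which follows from admitting youths with past depression, is a different question and is not settled here. Severity: should be fixed.

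**What to change.** - Delete the baseline-significance rule and the clause on empirically related variables as selection rules for the Aim 1 to 3 analyses.
- Before outcome data are seen by arm, fix one model containing the randomised risk level (as stratum or covariate), site, gender, baseline CES-D and past depressive episode. Risk level alone is not enough: in the simulation, gender plus risk level did no better overall than the protocol's rule, because the rule also picked up other prognostic variables.
- State in advance how practice is handled, for example by a shared frailty or a cluster-robust variance.
- Present baseline comparisons descriptively, without tests that feed the model.

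Other defensible covariate sets exist; what matters is that one is fixed. The cost is wording only: every variable is already planned for collection or known from the design, and the sample size is unchanged.
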